# Acupuncture for the treatment of diarrheal-predominant irritable bowel syndrome: study protocol for a pilot randomized controlled trial

**DOI:** 10.1186/s13063-021-05211-x

**Published:** 2021-04-07

**Keywords:** Irritable bowel syndrome, Acupuncture, Specific acupoints, Randomized controlled trial

## Abstract

**Background:**

Irritable bowel syndrome (IBS) is one of the most common functional gastrointestinal diseases. Although acupuncture has become a common alternative therapy for IBS, there is insufficient evidence for its effectiveness. This study was designed to assess the efficacy and feasibility of acupuncture in the treatment of IBS.

**Methods/design:**

This is a multicenter randomized controlled clinical trial. According to the ratio of 1:1:1, 90 patients with irritable bowel syndrome will be randomly divided into specific acupoints (SA) group, non-specific acupoints (NSA) group, and non-acupoints (NA) group. All patients will be treated with acupuncture 12 times within 4 weeks and followed up for 8 weeks. The primary outcome is the response rate, the percentage of patients whose average value of worst abdominal pain is 30% better and the days of loose stool is 50% less than the baseline, at week 4 after randomization. The secondary outcomes include the response rates at other time points, IBS Symptom Severity Scale (IBS-SSS), Patient Health Questionnaire-9 depression scale (PHQ-9), IBS-Quality of Life scale (IBS-QOL), IBS Adequate Relief (IBS-AR), Abdominal Pain Score, Abdominal Bloating Score, Bristol Stool Score (BBS), blinding assessment, and credibility evaluation. Adverse events will be monitored and recorded during the trial.

**Trial registration:**

Chictr.org.cn ChiCTR2000030670. Registered on 9 March 2020.

## Background and objectives

Irritable bowel syndrome (IBS) is a functional gastrointestinal disease [1], with abdominal pain, abdominal distension, changes in defecation habits, and stool irregularities as the main clinical manifestations [2]. The global prevalence of IBS is approximately 11% [3], while the prevalence in different regions of Asia ranges from 5.0% to 9.9% [4]. According to the Rome IV criteria [1], IBS were subgrouped into diarrheal-predominant IBS (IBS-D), constipation-predominant IBS (IBS-C), mixed IBS (IBS-M), and IBS unclassifable (IBS-U), among which IBS-D is the most frequently occurring subtype accounting for 40% [4]. Furthermore, IBS, one of the most common reasons for the abnormal state of life and work [5], increased the economic burden and impaired the life quality of patients [6, 7].

The pathophysiology of IBS is still poorly elucidated, thereby hampering the development of effective therapies for IBS [8]. Currently, available IBS treatments were broadly classified into drug therapies and other interventions, such as lifestyle and dietary modifications [9, 10]. Most IBS drugs are limited to the symptomatic treatment of specific symptoms of IBS which has no significant effectiveness on other related symptoms [11]. And lifestyle and dietary modifications were not uniformly effective across all patients. In this context, complementary and alternative medicine has shown promise [12]. As one of the treatments in complementary and alternative medicine, acupuncture is considered a beneficial alternative treatment for functional gastrointestinal disorders [13].

Acupuncture has been applied to gastrointestinal diseases in China for thousands of years, and its therapeutic effectiveness in IBS is being increasingly approved by more individuals [14]. Acupuncture is believed to alter visceral sensation and motility by interfering with the relevant mediators of the somatic nervous system and the central nervous system [15, 16]. In addition, studies have also shown that acupuncture can interfere with IBS from aspects of the brain-gut axis [17, 18] and the immune system [19]. However, the studies to date provided insufficient evidence to determine whether acupuncture is an effective treatment for IBS. A previous randomized controlled study assigned patients to receive either acupuncture (*n* = 22) or sham acupuncture (*n* = 21) concluded that “acupuncture in IBS is primarily a placebo response” [20]. But a total of 10 acupuncture/sham acupuncture sessions and sample size of 43 were considered insufficient, which may increase the likelihood of negative results. Furthermore, the acupoint is the key factor to determine the curative effect of acupuncture. Specific acupoints refer to the acupoints with special therapeutic function and naming in the meridians, which have specific treatment rules and wide applications. Comparing the therapeutic effects of different acupoint selection schemes is helpful to optimize the acupoint selection scheme and improve the clinical efficacy of acupuncture treatment, while the clinical efficacy among specific acupoints (SA), non-specific acupoints (NSA), and non-acupoints (NA) have not been revealed.

Therefore, we designed this clinical trial with the following two objectives: (I) explore the efficacy and safety of acupuncture in the treatment of IBS to guide the implementation of the large-scale trial; and (II) compare the different therapeutic effects of acupoint acupuncture groups and sham acupuncture group.

## Methods

### Trial design

This is a study protocol for a randomized, multicenter, clinical trial. Patients with IBS will be randomly assigned to the SA group, the NSA group, or the NA group in a 1:1:1 ratio (Fig. 1).

**Fig. 1 Fig1:**
[figure not shown]
The flow diagram of this trial

### Participants

This trial is an exploratory trial which will be conducted in four hospitals in China, including: (I) The Affiliated Hospital of Hebei University of Chinese Medicine; (II) the First Teaching Hospital of Tianjin University of Traditional Chinese Medicine; (III) the Teaching Hospital of Chengdu University of Traditional Chinese Medicine; and (IV) the Affiliated Hospital of Shandong University of Traditional Chinese Medicine. Patients who meet the IBS criteria of Rome IV will be recruited mainly through outpatient clinics, advertisements on hospital social media and newspapers. All patients will receive and fill in the informed consent before randomization.

#### Inclusion criteria

(I)Aged between 18 and 75 years (either sex);(II)Diarrheal-predominant irritable bowel syndrome (IBS-D); and(III)Type 6 or 7 of the Bristol Stool Form Scale appeared for at least 4 days and type 1 or 2 appeared for less than 4 days in the last 2 weeks; the average score of daily abdominal pain was ≥ 3 in the last week.

#### Exclusion criteria

(I)Patients with the following diseases: inflammatory bowel disease, microscopic colitis, celiac disease, Crohn’s disease, and other organic bowel diseases; diabetes mellitus and abnormal thyroid function; severe acute or chronic organic diseases, kidney or liver diseases;(II)History of previous abdominal surgery (appendectomy, hemorrhoidectomy, or polypectomy greater than 3 months post-surgery are allowed);(III)Pregnancy or lactation or history of alcohol and drug abuse;(IV)Treated with acupuncture in the last 6 months or participating in other clinical trials; and(V)Usage of antidepressant or IBS medication within 2 weeks before treatment, including traditional Chinese medicine (TCM) or proprietary Chinese medicine, antidiarrheal, antispasmodic, intestinal antibiotics, probiotics, and so on.

### Interventions

Before acupuncture treatment, licensed acupuncturists with at least 3 years of acupuncture experience will be trained in how to locate acupoints and non-acupoints, puncture and manipulate needles. All acupoints are localized according to the WHO Standard. Single-use sterile needles (0.30 mm in diameter and 30 mm in length or 0.30 mm in diameter and 25 mm in length; Hwato, Suzhou, China) will be used in the SA group and NSA group. To help maximize blinding of patients in the NA group, a blunt-tipped placebo needle will be used (similar to the Streitberger design [21]) which can provide patient-blinding effects with a similar appearance to conventional needles but no skin penetration [22]. And adhesive pads will be used in each group. Each patient will be scheduled to undergo 12 sessions of treatment, with each acupuncture lasting 30 min for 4 weeks (three sessions per week, every other day ideally). During the trial, patients will not be allowed to use other therapies or medications that have a therapeutic effect on IBS, such as traditional Chinese medicine (TCM) or proprietary Chinese medicine, antidiarrheal, antispasmodic, intestinal antibiotics, probiotics, and so on. Loperamide (Imodium, Xian Janssen Pharmaceutical Ltd., China) will be used as rescue medication under the guidance of gastroenterologists whenever necessary. The medication status and other non-irritable bowel syndrome drug applications of patients will be strictly recorded during the trial.

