### Outcomes

#### Primary outcome

In this trial, the response rate defined as the percentage of patients whose average value of worst abdominal pain is 30% better and the days of loose stool is 50% less than the baseline. The primary outcome is the response rate of week 4 after randomization. Patients will be asked to record daily IBS symptoms, including worst abdominal pain and stool type through Bristol Stool Scale. The score of worst abdominal pain in the preceding 24 h will be evaluated by visual analog scale (VAS), and the average value of worst abdominal pain will be calculated weekly.

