#### Secondary outcomes

##### The response rates at other time points

The response rate will also be measured at weeks 1, 2, 3, 8, and 12 after randomization.

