### Analytical methods

In this study, statisticians who blind to the group assignment will perform analyses using SPSS 22.0 statistical software. Continuous data will be represented by mean ± standard deviation (M ± SD) or median combined with interquartile range, whereas categorical data will be represented by frequency, constituent ratio, and percentage. Student’s *t* test or Wilcoxon rank-sum test will be used for the comparison of continuous variables, and chi-square test or Wilcoxon rank-sum test will be used for the comparison of categorical variables. *P* < 0.05 is considered to indicate statistical significance. Intention-to-treat (ITT) set will be used in all efficacy analysis, which will consist of all patients who have been randomized into groups, and the missing outcome data will be complemented using last observation carried forward (LOCF) or multiple imputation.

For the primary outcome, covariate analysis will be conducted applying a logistic regression model that includes baseline covariates for both pain score and stool consistency. A per-protocol analysis will be used for primary outcome as sensitivity analysis covering patients who complete ≥ 10 sessions and have no major protocol violations (taking other drugs during the trial, etc.).

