## Discussion

IBS is one of the most common functional gastrointestinal diseases and causes a considerable financial burden for individuals and society [10, 29]. This trial will evaluate the efficacy of SA versus NSA and NA in improving the symptoms of IBS. In this trial, we optimized the study design from the following aspects. First, this trial meets the methodological demand for adequate randomization, allocation concealment, and blinding of patients, outcome assessors, and statisticians. Second, patients will be provided 3 treatment sessions per week in the 4-week treatment phase, giving a total of 12 sessions. Compared with “6 treatment sessions over 3 weeks” in a previous study, the “dose” of acupuncture in our trial is more sufficient, which has been well practiced in clinical practice of China [30].

According to the TCM definition of IBS: “suppressed emotions and concerns would induce a liver qi stagnation, which in turn would lead to an attack of the liver on the spleen and stomach. The resulting weakness of the spleen leads to digestion problems. Furthermore, liver qi stagnation would block qi flow in the meridians, which would induce abdominal pain” [31, 32], the liver is an important organ related to IBS. Most IBS patients are accompanied by abnormalities of mood, such as anxiety, depression, and tension, which is in line with the clinical manifestations of liver dysfunction. The main symptoms of IBS are abdominal pain, constipation, and fatigue, which are common manifestations of spleen deficiency syndrome. Therefore, the additional specific acupoints in this trial were selected in accordance with the TCM treatment principles of invigorating the spleen and regulating the liver.

This study still has some noteworthy limitations. First of all, the acupuncturists cannot be blinded due to the nature of the acupuncture intervention. Second, when patients are unsatisfied with the treatment or cannot tolerate the symptoms of IBS, they may prefer to other treatment, which will increase the drop-out rate. In order to give patients a more comprehensive understanding of the trial, we have trained researchers to establish a good communication relationship with patients. Third, the follow-up of 8 weeks is short, which may affect the outcomes of this trial. We will conduct the large-scale trials with long-termfollow-up of patients.

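### The primary responder rule sets no condition for rescue loperamide, so under ITT a patient who meets the pain criterion can count as a responder because the drug firmed the stools

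*Protocol article*

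**What the plan says.** All references are to the protocol article.

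- **Interventions.** During the trial "patients will not be allowed to use other therapies or medications that have a therapeutic effect on IBS"; antidiarrheals are among the examples listed. The exception follows at once: "Loperamide (Imodium, Xian Janssen Pharmaceutical Ltd., China) will be used as rescue medication under the guidance of gastroenterologists whenever necessary". No limit on dose, frequency or timing is given. Use is documented: "The medication status and other non-irritable bowel syndrome drug applications of patients will be strictly recorded during the trial".
- **Exclusion criteria.** "Usage of antidepressant or IBS medication within 2 weeks before treatment" is an exclusion, and the list that follows includes antidiarrheals. The stool diary that precedes randomization also covers 2 weeks (Sequence generation).
- **Primary outcome.** A responder at week 4 is a patient whose "average value of worst abdominal pain is 30% better and the days of loose stool is 50% less than the baseline". The abstract gives the same two conditions.
- **Secondary outcomes.** "The response rate will also be measured at weeks 1, 2, 3, 8, and 12 after randomization".
- **Analytical methods.** "Intention-to-treat (ITT) set will be used in all efficacy analysis, which will consist of all patients who have been randomized into groups". The logistic model for the primary outcome adjusts for baseline pain and stool consistency. A per-protocol sensitivity analysis requires at least 10 sessions and no major violation, with the taking of other drugs as the example.

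**The concern.** Loperamide belongs to a drug class that the protocol itself bans because it affects IBS, and it acts directly on one half of the primary endpoint. Loose-stool days in a week when the drug is allowed are compared with a baseline from which such drugs are excluded. The rule has no term for rescue, so the plain reading is that a firm-stool day on loperamide counts like any other firm-stool day. The text does not say this in words. It follows from applying the two conditions as stated.

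The stake is interpretation. The response rate is used to compare acupuncture schemes, and this route credits a drug effect to them. If rescue differs by arm, the difference between arms is also affected. Under Sample size, the results are meant to feed the sizing of a later trial.

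**Working it through.** **1. The plan's own figures.** 3 arms × 30 = 90, as stated. The article gives no response rate, rescue rate, effect size or power, so no stated figure can be contradicted. All rates below are assumptions.

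**2. Do the other provisions close the route?**
- ITT keeps rescued patients in the analysis.
- The regression covariates are baseline values, so rescue is not in the model.
- LOCF or multiple imputation acts on missing data, and a loperamide day is not missing.
- The per-protocol set may exclude some users. But loperamide is permitted, so it is not clearly a violation, and removing users after randomization is selective.

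**3. How many firmed days are enough?** Assume that baseline is expressed per week (Primary outcome does not say) and that the stool half means at least 50% fewer days. For a baseline of b days, the allowed number is b/2 rounded down. With no real change, firmed days needed = b − allowed.

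| Weekly baseline | 2 | 3 | 4 | 5 | 6 | 7 |
|---|---|---|---|---|---|---|
| Allowed | 1 | 1 | 2 | 2 | 3 | 3 |
| Firmed days needed | 1 | 2 | 2 | 3 | 3 | 4 |

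Inclusion requires at least 4 loose-stool days in 2 weeks, that is 4/2 = 2 per week. At that minimum, one firmed day meets the stool half.

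**4. Effect on response rates.** Observed rate = p + r·q·c, where
- p is true response without the drug: SA 0.50, NA 0.25;
- r is the share of the arm rescued in week 4 who would miss the stool half off drug;
- q is the share of these who meet the pain half, 0.3 to 0.5;
- c is the share of those whose stool half is met because of loperamide, 0.5 to 0.8.

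So q·c runs from 0.3 × 0.5 = 0.15 to 0.5 × 0.8 = 0.40.

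| r, SA / NA | Low q·c | High q·c | Change from 25 points |
|---|---|---|---|
| 0.05 / 0.20 | 0.5075 − 0.2800 = 0.2275 | 0.5200 − 0.3300 = 0.1900 | −2.25 to −6.0 |
| 0.15 / 0.05 | 0.5225 − 0.2575 = 0.2650 | 0.5600 − 0.2700 = 0.2900 | +1.5 to +4.0 |
| 0.10 / 0.10 | 0.515 − 0.265 = 0.25 | 0.540 − 0.290 = 0.25 | 0; both rates 1.5 to 4 points too high |

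In patients this is 30·r·q·c, from 30 × 0.05 × 0.15 = 0.225 to 30 × 0.20 × 0.40 = 2.4 extra responders per arm. With q = 0 there is no effect.

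**5. Does equal use cancel?** Only if q and c are also equal across arms. Suppose instead that patients who meet only the pain half are 15% in SA and 25% in NA, with rescue in 10% of them in both arms. The rates become 0.50 + 0.15 × 0.10 × c and 0.25 + 0.25 × 0.10 × c, a difference of 24.5 points (c = 0.5) to 24.2 points (c = 0.8). In this model, rescue of 10% against 30% gives 22.0 to 20.2 points. An extreme 10% against 50% gives 19.5 to 16.2.

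**6. Against the pilot's precision.** SE = √(0.5 × 0.5/30 + 0.25 × 0.75/30) = 0.121, and 1.96 × 0.121 = 0.237, about 24 points.

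**7. Next trial's size.** n per arm = (1.960 + 0.842)² × [p₁(1 − p₁) + p₂(1 − p₂)] / (p₁ − p₂)², for 80% power and two-sided 5%. The true rates give 55. The rates in step 4 give 69 to 103 (0.05/0.20), 42 to 50 (0.15/0.05) and 56 to 58 (equal).

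**The case against.** **A journal article condenses, and the SAP is not shown.** How rescue days enter a diary endpoint is often settled there. This stands as a caution: a rescue rule may exist elsewhere. But the article states who is a responder, twice and without a rescue term, so adding one changes the stated rule and does more than supply detail.

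**Counting observed symptoms whatever rescue was taken is a recognised treatment-policy choice.** True, and no sentence says that rescue effects are to be removed. It remains a poor default where the rescue drug acts directly on one component and the result is read as the effect of acupuncture.

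**The route is narrow.** It needs rescue in the assessment week, the pain half met, the stool half missed off drug, and the stool half met on drug. This stands and limits the weight of the point.

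**The next-trial figures distort planning only if that trial changes its endpoint or rescue policy.** This also stands. If both are kept, the observed rates are the right planning inputs.

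Three stronger readings are tempting, and the article supports none of them:
- *The permission contradicts the ban.* A general ban with one named, supervised and recorded exception is coherent.
- *The comparison is biased in a known direction.* The Discussion says that "when patients are unsatisfied with the treatment or cannot tolerate the symptoms of IBS, they may prefer to other treatment", but about drop-out. Nothing states how rescue will differ by arm, and step 4 shows that the shift can go either way.
- *Equal rescue would make the issue harmless.* Both rates would still be too high, and the difference stays fixed only under the added conditions in step 5.

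**Conclusion.** The point holds as a modest, cheaply corrected weakness in the primary endpoint. Applied as written under ITT, the rule can classify a patient who meets the pain criterion as a responder because of loperamide, and the same applies at weeks 1, 2, 3, 8 and 12. The per-protocol analysis is only a partial safeguard.

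Size and direction are unknown. Under the main assumed rates with unequal rescue, the arm difference moves by about 1.5 to 6 points. The extreme case in step 5 reaches 25 − 16.2 = 8.8. All of these are well inside the half-width of about 24 points, so a reader should not infer that the pilot's comparison is invalidated. Confidence is medium, because every rate is assumed and a fuller document may already deal with rescue.

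**What to change.** - In the primary responder derivation, count each assessment-week diary day with recorded loperamide use as a loose-stool day. Apply the same rule at weeks 1, 2, 3, 8 and 12.
- Report rescue use by arm.
- Keep the rescue-ignored endpoint as a sensitivity analysis.
- State whether loperamide counts as a violation in the per-protocol set.
- Use next-day carry-over only as a stricter sensitivity analysis. Its length has no basis in the article, and one mid-week dose would then count as 2 loose days, which fails anyone with a weekly baseline of 2 or 3 (1 allowed).
- If dates were not recorded, treat the stool half as unmet in any week with loperamide, again only as a stricter sensitivity analysis.

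The cost is one sentence and one derived variable. Medication status is already recorded, though the article does not promise dates, and with completion expected by the end of March 2021 a new date field may come too late. The rule should be fixed while the statistician is still blinded.

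Response rates become somewhat lower, and some true responders who took loperamide will be counted as non-responders. With one dose day, a baseline of 2–3, 4–5 or 6–7 leaves 0, 1 or 2 other loose days. The same-day rule cannot be harsher than the week-level rule. If 10% of true responders took any dose that week (assumed), the week-level rule gives 0.50 × 0.9 = 45% and 0.25 × 0.9 = 22.5%.

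The same-day rule does not close the route fully if a dose also firms the next day. At a baseline of 2, one dose could firm both days, and 2 − 2 + 1 = 1 still passes. The carry-over sensitivity analysis addresses this.

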#### Specific acupoints group

The acupoints used in this group are composed of fixed acupoints and optional acupoints. Fixed acupoints include *Tianshu* (ST25), *Zhongwan* (RN12), *Guanyuan* (CV4), *Zusanli* (ST36), and *Shangjuxu* (ST37), which are commonly used in IBS patients. Optional acupoints will be selected based on the traditional Chinese acupuncture diagnosis of patients by the acupuncturist, such as *Taichong* (LR3) for syndrome of liver depression and spleen deficiency, *Sanyinjiao* (SP6) for syndrome of spleen deficiency and dampness obstruction, and *Neiting* (ST44) for syndrome of spleen-stomachdamp-heat. After sterilization, the acupuncturist will insert single-use sterile needles into the deep tissue layers through adhesive pads of acupoints. Following needle insertion, small, equal manipulations of twirling, lifting, and thrusting will be performed on all needles to reach *de qi* (a component sensation, including soreness, numbness, distension, and heaviness). Acupuncture Locations and exhibited in Table 1.

**Table 1 Tab1:** Locations of acupoints for SA group

	Acupoint	Location
Fixed acupoints of SA group	*Tianshu* (ST25)	On the horizontal line of the navel, 2 cun^a^ beside the anterior midline
	*Zhongwan* (RN12)	On the anterior midline of the upper abdomen, 4 cun superior to the navel
	*Guanyuan* (CV4)	On the anterior midline of the abdomen, 3 cun inferior to the navel
	*Zusanli* (ST36)	3 cun directly below ST35, and one finger-breadth lateral to the anterior border of the tibia
	*Shangjuxu* (ST37)	On the anterolateral aspect of the leg, 6 cun inferior to the ST35, and one finger-breadth lateral to the anterior border of the tibia
Optional acupoints of SA group	*Taichong* (LR3)	In the depression anterior to the junction of the first and second metatarsal bones
	*Sanyinjiao* (SP6)	On the tibial aspect of the leg, posterior to the medial border of the tibia, 3 cun superior to the prominence of the medial malleolus
	*Neiting* (ST44)	On the instep, between the second and third toes of the red and white flesh behind the webbed margin

^a^1 cun (≈20 mm) is defined as the width of the interphalangeal joint of the patient’s thumb

